### Setting and participants

The study will be carried out in 60 English general practices that contribute data to the Royal College of General Practitioners (RCGP) Research and Surveillance Centre (RSC) Network^24 25^ and use the EMIS Web EHR system. The RCGP RSC includes general practices in England. A full list of NHS Clinical Research Networks from which practices will be recruited may be found in online supplementary appendix A.

10.1136/bmjopen-2020-038562.supp1Supplementary data

#### Inclusion and exclusion criteria

The inclusion criteria for general practices are as follows:

Practice is actively contributing data to the RCGP RSC.Utilises EMIS EHR systemData available for the previous 24 months.

The exclusion criteria for general practices are:

Practices that express an interest, but are not fully set up for data extraction.Any practice already deploying the E-SN toolkit.

All patients over the age of 18 at participating practices are eligible for inclusion in the study, unless they have opted out of data sharing.

### Recruitment

The RCGP RSC network will identify potentially eligible practices and circulate the details of the study before and during the recruitment period. Practices will also be approached directly by the RCGP RSC Practice Liaison Officers (PLOs), who regularly visit practices to monitor their data quality and inform about current open studies. Expressions of interest will be obtained from all interested practices. An additional 12 practices will be identified to account for potential drop-outs during the study. All practices will be recruited at the start of the study prior to randomisation and implementation of the intervention.

General practices will receive reimbursement of up to £500 per practice for participation in the 12-month stepped-wedge intervention study.

### Randomisation and blinding

The eligible practices will be ranked according to their list size from smallest to the largest by the RCGP RSC. These will then be stratified into 10 strata (by list size) such that each strata contains the same number of practices. This is based on the allocation of 10 practices per step. Practices will be randomised in blocks of 10 to the timing of activation of the E-SN toolkit and will crossover in these blocks to the activated phase every 2 months. Therefore, practices will contribute between 2 months and 12 months of E-SN toolkit-activated time (figure 1).

A statistician ([name], Nuffield Department of Primary Care Health Sciences, University of Oxford) who is independent to the intervention development and implementation will produce a stratified randomisation schedule so that within each strata, practices are randomly allocated to each of the six steps, with some replacement practices. The random sequence will be generated using R software. The allocation will be undertaken for all practices at the same time. Where replacement practices are required, these will be taken from the same strata where possible. If no replacement practices from the same strata are available a coin toss will determine whether the next highest or lowest strata will be used to provide replacement practices.

Given the practice change nature of the intervention, clinicians and practice managers will be aware when their practice has switched to the intervention period. Consulting patients providing outcome data will not be informed of the experimental nature of the E-SN toolkit activation and therefore will be blind to the stage of study occurring in the practice they attended. Study personnel involved in extracting outcome data will be blind to the allocated order of the delivery of the intervention across the practices. All data management of extracted data to calculate the outcome measures will be conducted blinded to the timing of switching to intervention. Similar methods have been used in other implementation SW-CRCTs.^26^

### Intervention

The intervention consists of activation and the implementation of the E-SN toolkit at participating practices. All practices will receive training in the use of the E-SN toolkit from RCGP PSC PLOs prior to their switching date. Clinicians will be able to use the E-SN templates at their own discretion during the active period, with no requirements on which patients should or should not receive safety netting. Clinical care of patients will continue as normal throughout the study.

The E-SN toolkit uses a templates to track cancer events like referrals, direct access tests and monitoring of low risk through read codes attached to diary entries. Expired diary entries would be identified using automated searches and actioned by the administration lead as appropriate. If an event was complete, for example, normal scan results done in 2 weeks and result back—then the diary entry is closed, resolving the episode. The E-SN toolkit has extra features such as popup alerts to remind any user there is an open diary entry and also allows the E-SN toolkit to popup automatically if a relevant code is used in the clinical records.

Further details and demonstration video are available from: https://www.uclh.nhs.uk/OurServices/ServiceA-Z/Cancer/NCV/MICa/Pages/Primarycareimprovement.aspx

Practices will all be encouraged to adhere to the schedule for switching and will receive part-payment for study initiation and then full payment when they adhere to the activation schedule.

### Data extraction

Data extractions from all participating practices will correspond to two major time points: at the start of the introduction to the stepped wedge implementation of the E-SN toolkit, and at the end of the stepped wedge period (12 months later). At these two time points, consultation data from the participating practices will be obtained for the previous 24 months. Data from the previous 24 months are required to identify cancers detected in 12 months prior to start, plus the first recorded symptom of cancer during the primary care interval, allowing for this interval to cover up to a year prior to diagnosis.

Records from all patients who are adults aged 18 years and above, registered at participating practices and who have not opted out of sharing data for research purposes will be extracted. Pseudonymised patient information will include: demographic information of age, sex, dates of clinical consultations; coded consultation data for symptoms, diagnoses, tests ordered and referrals made within the consultation records. Where a definitive diagnosis has been made (for cancer and non-cancer conditions), the clinical features recorded in the year prior to diagnosis will be captured. These actions will be achieved by extraction of the EHR rather than by hand searching notes.

Practices will be asked to search for open diary entries every week during the intervention period, and to download and save these to an Excel spreadsheet (locally). The central study research team will use these spreadsheets to track which diary entries are closed during the course of the intervention.

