**Trial registration number:**

ISRCTN15913081; Pre-results.

Strengths and limitations of this studyThe safety-netting toolkit being evaluated is already implemented and integrated in the Egerton Medical Information System (EMIS) Web, a brand of electronic health record (EHR), but is rarely used.Data collection will be carried out primarily through existing automated links between the practice EHR and the RCGP Research and Surveillance Centre, surveillance system, thereby limiting the additional research workload for participating practices.We are reliant on the cancer diagnosis, generally made in specialist care, being recorded in the primary care EHR system in a consistent and timely manner.

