**Figure 2 F2:**
[figure not shown]
Diagram showing the definitions of time-based outcomes.

**Table 2 T2:** Outcomes, measures and time periods of measurement for primary and secondary outcomes

Outcome	Measure	Inactive study period	Active study period	Template activations only
Primary outcome				
Primary care interval for cancer diagnoses	Measured as the no of days between first recorded symptoms of cancer (within the year prior to diagnosis) and subsequent referral for secondary cancer care	X	X	
Secondary outcomes				
Proportion of cancers diagnosed after emergency presentation	Proportion of cancers for which diagnosis is made prior to referral, including following A&E or inpatient episodes. Where there is uncertainty regarding the route of diagnosis, the RCGP RSC network will contact the practice in an attempt to augment the data. Algorithms will also be developed to identify emergency presentations of cancer.	X	X	
Recorded new diagnoses in those who have a template activated	By cancer site and stage, and non-cancer diagnoses. Coded entries for all alternative diagnoses where the E-SN toolkit has been activated will be identified.		X	X
Total time to diagnosis (from first recorded symptom to definitive diagnosis)	Measured from first recorded symptom of cancer (within the previous year) to definitive diagnosis for all cancers diagnosed, and for all patients with an activated template	X	X	X (for non-cancer diagnoses)
No of GP consultations/patient between first record of symptom and cancer referral	Measured as no of primary care consultations between the first recorded symptoms (within the year prior to diagnosis) and subsequent referral, per patient.	X	X	
Rates of patients completing direct access cancer investigations	Measured as the no of patients undergoing direct access cancer investigations (according to those specified in referral guidelines NG12) in each period divided by the person years of observation for that period.	X	X	
Rates of patients referred for cancer	Referrals rates via 2-week wait, urgent, and routine routes for all patients referred for specialist opinion to a secondary care cancer specialist	X	X	
Timing of template activation	Measured as the no of days between first recorded symptoms (within the year prior to diagnosis), and template activation and the no of days between template activation and subsequent referral.		X	X

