Template activation rate among consulting patients	Measured as the number of patients with an activated template divided by the no of patients consulting, in each time period. Both total rate and rate stratified by individual GP will be measured.		X	X
Proportion of diary entries that were completed	Measured as the no of diary entries that were completed divided by the number of diary entries that were opened.		X	X
Reason for template activation	The coded reasons for activating the template, Based on 20 high level READ codes		X	X
Symptoms leading to direct access to investigation	All symptoms recorded in patients undergoing direct access cancer investigations	X	X	
Recorded vague symptoms in the template	All symptoms recorded within the template.		X	X
Demographic details of patients with activated templates	Age and sex of patients that had a template activated during the course of the trial.		X	X
GP type completing templates	Descriptive data on the type of GP that first activated the template (eg, partner, locum, trainee)		X	X
Diagnostic codes in patients with activated templates	Diagnoses recorded after the activation of template.		X	X

E-SN, electronic safety-netting; GP, general practitioner; RSC, Research and Surveillance Centre; RSC, Research and Surveillance Centre.

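### The final extraction has no lag after the wedge, so template-only secondary outcomes that run forward from activation are incompletely observed

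*Protocol article*

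**What the plan says.** The Data extraction section names two downloads, one at the start of the wedge and one "at the end of the stepped wedge period (12 months later". Other parts of the article agree that nothing later is used:

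- The Statistical analysis section limits the data to the study period and the year before it.
- Table 1 goes further back but has the same upper end.
- The study timeline (end of the Study design section) goes from the 12-month intervention period directly to 3 months of analysis.
- The extra downloads in the COVID-19 section serve a separate before-and-after analysis and are not said to extend follow-up.

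Table 2 includes these template-patient outcomes, all of which depend on events after activation:

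- recorded new diagnoses, and diagnostic codes, described as "Diagnoses recorded after the activation of template";
- days from template activation to referral;
- total time to diagnosis, taken "to definitive diagnosis for all cancers diagnosed, and for all patients with an activated template", where only the non-cancer part is marked as template-only;
- diary entries completed as a proportion of those opened, tracked from weekly spreadsheets that practices save during the intervention period.

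The article states no minimum follow-up after activation and no activation cut-off. Its list of limitations says that the study is "reliant on the cancer diagnosis, generally made in specialist care, being recorded in the primary care EHR system", and adds that this must be consistent and timely.

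**The concern.** An outcome counted forward from activation needs time in which to happen and to be coded. In a stepped wedge the number of active practices rises until the end, so the largest share of activations can be expected close to the data cut-off. Patients whose referral, diagnosis or diary closure comes after month 12 then count as not having had it.

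Two distortions follow. Proportions (diagnoses after activation, diary entries completed) are too low because they are right-censored but not treated as such. Intervals computed only in patients with the event are too short because slow events are cut off. These outcomes have no inactive phase, so no comparison or period effect can cancel the loss.

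At stake is the description of how the toolkit is used and what follows from its use. The Sample size section expects benefit in patients with vague symptoms, who are less likely to be referred at once. Theirs are the events most likely to fall after the cut-off.

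**Working it through.** **Inputs from the protocol article.** The setting: "The study will be carried out in 60 English general practices". The allocation: "Practices will be randomised in blocks of 10 to the timing of activation of the E-SN toolkit", with a crossover every 2 months. The number of steps: "practices are randomly allocated to each of the six steps". The final extraction is at month 12.

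**Reproducing the stated exposure.** Blocks that start at months 0, 2, 4, 6, 8 and 10 have 12, 10, 8, 6, 4 and 2 active months. This matches the statement that "practices will contribute between 2 months and 12 months of E-SN toolkit-activated time".

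**Where the active time falls.** One practice-step is one practice active for one 2-month step.

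| Step | Active practice-steps | Share of 210 | Months left to extraction |
|---|---|---|---|
| 1 | 10 | 4.8% | 10–12 |
| 2 | 20 | 9.5% | 8–10 |
| 3 | 30 | 14.3% | 6–8 |
| 4 | 40 | 19.0% | 4–6 |
| 5 | 50 | 23.8% | 2–4 |
| 6 | 60 | 28.6% | 0–2 |

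The last two steps hold (50 + 60)/210 = 52.4%. Mean follow-up over all active time is (10×11 + 20×9 + 30×7 + 40×5 + 50×3 + 60×1)/210 = 910/210 = 4.3 months. These are shares of practice-time. They are shares of activations only if activations are spread evenly over active time, which is assumed below.

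**Share of eventual events not seen, assumed exponential times.** The article gives no time from activation to event, so medians of 30, 60 and 90 days are assumptions. With median m, the scale is λ = m/ln 2. In a step of length D = 365/6 = 60.8 days whose shortest follow-up is a days, the share missed is (λ/D)·[exp(−a/λ) − exp(−(a+D)/λ)].

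- Last step, m = 30: λ = 43.3 and a = 0, so (43.3/60.8)·(1 − exp(−60.8/43.3)) = 0.712 × 0.755 = 0.54.
- All steps, m = 30: the shares missed in steps 1 to 6 are 0.000, 0.002, 0.008, 0.032, 0.132 and 0.537. Weighted by 1 to 6 and divided by 21, they give 0.19.
- A 90-day lag multiplies the loss by exp(−90/λ), which is 0.125, 0.354 and 0.5 for the three medians.

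| Assumed median (days) | Missed, last step | Missed, overall | Median seen (days) | Missed overall with 90-day lag |
|---|---|---|---|---|
| 30 | 54% | 19% | 24 | 2% |
| 60 | 72% | 34% | 39 | 12% |
| 90 | 80% | 45% | 48 | 22% |

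The medians seen come from simulation (2 million draws) and describe an interval that starts at activation, such as activation to referral.

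**The same calculation with the protocol's own intervals.** The Sample size section gives primary care intervals: all cancers, median 5 days, upper quartile 27 and a 90th centile of about 60; lung cancer, median 14 and upper quartile 45. Weibull curves through these points, used as a stand-in for activation to referral, give:

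| Curve | Missed, last step | Missed, overall |
|---|---|---|
| All cancers, median and 90th centile | 25% | 9% |
| All cancers, median and upper quartile | 28% | 13% |
| Lung cancer, median and upper quartile | 39% | 16% |

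**The case against.** The strongest reply is that these outcomes are descriptive, secondary and without a comparator, so they cannot bias the estimated effect. That stands.

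Three stronger readings are tempting, and the article does not support them:

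- **That the trial's main result is biased.** The primary care interval looks back from a diagnosis. Late coding can lose some cases near month 12, but the model has a fixed effect for time, which absorbs a loss shared by all practices in a period. In the last step all 60 practices are active, so that step has no concurrent contrast to distort. The argument assumes that coding delay does not depend on activation.
- **That total time to diagnosis has no comparator.** It starts at the first recorded symptom, and Table 2 measures it in both phases for cancers. Only the non-cancer part in template patients belongs to this point.
- **That activation-to-diagnosis time is a reported outcome that would come out too short.** It is not an outcome. The interval from activation that Table 2 reports is activation to referral.

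It can also be said that the 30- to 90-day medians have no source in the article, that late coding is already declared as a limitation, and that censoring belongs in the analysis plan, which is not shown. The first is right, hence the range. The other two do not dispose of the point. Declaring the limitation allows no time for coding. The extraction date is fixed in the protocol, and an analysis plan cannot recover events after it; it can only allow for their absence. The completed-over-opened ratio for diary entries is also fixed as stated. The rule that a missing referral means no referral concerns the primary care interval, so little weight is put on it here.

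**Conclusion.** The point holds for the template-only secondary outcomes that depend on events after activation, and only for those. The direction does not depend on the assumed distribution: diagnoses, referrals and diary completions are under-counted, and intervals among patients with the event are too short. The loss is greatest in the last step and smaller, but not zero, in earlier ones.

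The design count (28.6% of active practice-time with under 2 months of follow-up, 52.4% with at most 4) follows from the article alone. The size of the loss does not. It rests on evenly spread activations and on an assumed activation-to-event time, and ranges from about 9% to 16% of referrals under the protocol's own intervals to about 19% to 45% of events under the longer assumed times. A reader should not infer that the primary comparison is compromised. This is a worthwhile, inexpensive improvement and not a flaw in the trial's main inference.

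**What to change.** Either change suffices for the outcomes taken from the automated download:

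- **Move the download.** Keep the 12-month wedge as the analysis window and run the final automated extraction about 3 months after it ends. The cost is about 3 months on the 18-month timeline. Under the assumed medians this cuts the overall loss from 19%, 34% and 45% to about 2%, 12% and 22%, so follow-up should still be reported by time since activation.
- **Keep the date and change the analysis.** Report template-forward outcomes as cumulative incidence by days since activation, censored at extraction. Or restrict them to activations at least 90 days before extraction and count events within 90 days of activation. The cost is wording and, for the restriction, fewer activations. Taking 90 days as 3 months, it drops all of step 6 and half of step 5, (60 + 25)/210 = 40.5% of active practice-time.

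Diary completion needs the second approach in either case. Its weekly tracking ends with the intervention period, and a later automated download does not extend it.

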Key Secondary Outcomes	Proportion of cancers diagnosed after emergency presentation measured during inactive and active E-SN phases. Recorded new diagnoses in those who have a template activated, measured by cancer site and stage, and by non-cancer diagnosis, during the active E-SN stage. Total time to diagnosis measured from first recorded symptom to definitive diagnosis for all cancer diagnoses during the inactive and active E-SN phases and all diagnoses with template activation during the active E-SN phase No of GP consultations/patient between first record of symptom and cancer referral, measured during the inactive and active E-SN phase Rates of patients completing direct access cancer investigations measured during the inactive and active E-SN phase Rates of patients referred measured as 2-week wait, urgent, and routine, during the inactive and active E-SN phase Timing of template activation within the primary care interval (from first symptom to referral) measured during the active E-SN phase Template activation rate among consulting patients, both total and stratified by individual GP, measured during the active E-SN phase The proportion of diary entries completed measured during the active E-SN phase The reason for template activation measured based on 20 high-level READ codes during the active E-SN phase Symptoms leading to direct access to investigations measured during the active E-SN phase Recorded vague symptoms in the template measured during the active E-SN phase Demographic details of patients with activated templates measured during the active E-SN phase GP type completing template (eg, partner, locum, trainee) measured during the active E-SN phase Diagnostic codes in patients with activated templates measured during the active E-SN phase

EMIS, Egerton Medical Information System; E-SN, electronic safety-netting; GP, general practitioner.

The anticipated length of the study is 18 months. This consists of 3 months recruitment, followed by a 12-month period during which time the intervention will be introduced, and 3 months for analysis.

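### The weekly list of open diary entries does not match the outcome of entries completed divided by entries opened: it misses entries closed between searches and may count vanished entries as completed, so the net direction of bias is unknown

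*Protocol article*

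**What the plan says.** Table 2 of the protocol article (Secondary outcomes) defines the proportion of diary entries completed as "Measured as the no of diary entries that were completed divided by the number of diary entries that were opened". Table 1 lists it among the key secondary outcomes: "The proportion of diary entries completed measured during the active E-SN phase".

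The Data extraction section describes how diary entries are followed: "Practices will be asked to search for open diary entries every week during the intervention period". The result is saved locally in a spreadsheet. The section continues: "The central study research team will use these spreadsheets to track which diary entries are closed during the course of the intervention". No other source for closure is named.

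The same section describes the central extract from the health record. It covers age, sex, consultation dates and "coded consultation data for symptoms, diagnoses, tests ordered and referrals made within the consultation records". Opening and closing dates of diary entries are not in that list.

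The Intervention section says that entries carry Read codes ("monitoring of low risk through read codes attached to diary entries") and that an entry is closed once its event is complete. Its example is "normal scan results done in 2 weeks and result back". The article gives no distribution of the time that entries stay open.

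**The concern.** The definition needs every entry opened and, for each, whether it was completed. The stated instrument records only which entries are open on the search day. The two differ in two ways.

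- **Quick closures are unseen.** An entry opened on a Tuesday and closed on the Friday of the same week, with no search in between, is on no list. It is lost from the numerator and, if the lists also supply the denominator, from there too. All such entries were completed, so the loss can only lower the proportion.
- **Other exits look like closures.** An entry can also leave the open list because it was deleted or because the patient died or left the practice. The section mentions no completion code or closing reason that would separate these from completion. Counting them as completed raises the proportion.

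The toolkit exists to make sure that follow-up is tracked and closed, and this outcome measures that directly. It will be read when the team asks how well the toolkit was used, particularly if the primary result is null. Entries that were never captured cannot be recovered by any later analysis.

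**Working it through.** The article states no figure for this outcome, so there is none to reproduce. The check derives the direction of each mechanism and illustrates its size.

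**Inputs**
- Search interval: 7 days (Data extraction).
- Outcome: completed / opened (Table 2).
- True proportion completed, p: not given; 50%, 80% and 90% are assumed.
- Mean time to closure, m: not given; 7, 14 and 28 days are assumed. The one example in the Intervention section is about 2 weeks.

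**Mechanism 1: entries closed between searches.** Let q be the share of completed entries that appear on no list. If the lists supply both numerator and denominator:

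observed = p(1 − q) / [p(1 − q) + (1 − p)]

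This is below p whenever q > 0 and 0 < p < 1, whatever the closure-time distribution.

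For the size, let opening times be uniform over the week and time to closure exponential with mean m:

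q = 1 − (m/7)(1 − exp(−7/m))

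- m = 7: q = 1 − 1 × 0.632 = 36.8%
- m = 14: q = 1 − 2 × 0.3935 = 21.3%
- m = 28: q = 1 − 4 × 0.2212 = 11.5%

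A simulation of one million entries per scenario gave 36.7%, 21.3% and 11.5%.

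| True p | m = 7 | m = 14 | m = 28 |
|---|---|---|---|
| 50% | 38.7% | 44.0% | 46.9% |
| 80% | 71.7% | 75.9% | 78.0% |
| 90% | 85.1% | 87.6% | 88.8% |

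Two other closure patterns show how far the size depends on the assumption:
- Closures spread evenly over 0 to 14 days: q = 3.5/14 = 25%, and a true 80% reads 0.60/0.80 = 75%.
- No entry closed within 7 days: every entry meets at least one search, q = 0, and there is no loss.

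**Mechanism 2: other exits counted as completed.** Let r be the share of uncompleted entries that leave the list through deletion, death or deregistration. The numerator gains r(1 − p). The two mechanisms cancel when

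r(1 − p) + p(1 − q) = p(1 − pq), that is, r = pq.

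For p = 80% the break-even r is 29.4%, 17.0% and 9.2% at m = 7, 14 and 28. Below it the net bias is downward, above it upward. The article gives neither q nor r.

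**Comparison between practices.** At equal true completion of 80% and no other exits, a practice with m = 7 reads 71.7% and one with m = 28 reads 78.0%.

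**The case against.** The strongest reply is that the lists need not be the only source. The article makes the coded record the principal data source (Data management) and says that outcome data come from coded entries in it (Informed consent). Diary entries carry Read codes. The extract list also omits template activation, which several Table 2 outcomes need, so that list is probably not exhaustive. If opened entries were counted from the record and any entry absent from the next open list were read as closed, no quick closure would be lost.

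This shows that a repair is feasible, but the article does not state that rule. With a record-based denominator and an unlisted entry treated as not completed, observed = p(1 − q), and a true 80% reads 50.6%, 63.0% or 70.8%. With absence read as closed, the first mechanism disappears but the second stays: observed = p + r(1 − p). For p = 80% and r = 17% that is 0.80 + 0.17 × 0.20 = 83.4%.

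The reply is also right that the exponential model puts the most closures in the first days, whereas entries are reminders attached to tests, referrals and monitoring that may stay open for weeks. The size could therefore be small or nil.

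Three stronger readings are tempting, and the documents do not support them:
- **That the proportion is biased downwards overall.** Only the first mechanism has that sign, and the second opposes it.
- **That practices closing entries fastest score worst.** This needs equal true completion. A fast practice (m = 7, true 90%) reads 85.1% and a slow one (m = 28, true 80%) reads 78.0%, so the order is kept. The article plans no ranking of practices on this outcome.
- **That the trial's main result is affected.** This is one of 15 secondary outcomes, is measured only in the active phase, and enters neither the primary outcome nor the sample size.

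**Conclusion.** The point holds as a mismatch between a stated collection method and a stated definition. It is more than a detail left to the full protocol or the analysis plan, because the article fixes the method and data lost at collection cannot be restored later.

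The sign of each mechanism follows from the article's text, provided that the weekly lists are the source of closure, as the article says, and that leaving the list is taken as closure. The size rests on assumed closure times: for a true 80%, a loss of about 8, 4 or 2 percentage points at mean 7, 14 or 28 days, and none if no entry closes within a week. Other exits offset this by an unknown amount, so the net direction is open. What can be said is that the measure partly reflects speed of closure, so that at equal true completion, and with other exits alike, faster practices score lower. The matter is worth correcting, but it is confined to a descriptive process outcome.

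**What to change.** Change the Data extraction section in one of two ways:

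1. The weekly saved search returns all toolkit diary entries opened or closed since the last search, with opening date, closing date and closing code.
2. The end-of-study extraction includes all Read-coded toolkit diary entries with both dates and the closing code.

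In either case, state that the denominator is all entries opened, and count an entry as completed only where completion is recorded. Report entries that ended through deletion, death or deregistration separately.

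The cost is a small change to the search or extraction specification. Nothing in the article suggests that it needs extra visits or staff. It has to be in place before the lists are collected, unless the record keeps both dates and the second route is used.
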